Upon the above rationale, the upcoming question is that what benefits of cardiopulmonary rehabilitation can be delivered to ECMO-supported patients. For clinicians, ECMO weaning is particularly challenging and annual ECMO mortality has been reported to be approximately ranged 40–70% (10, 11). According to our experience, delayed ECMO weaning also demonstrated worse functional prognosis and impaired health-related quality of life (HRQoL). Previous studies have documented that rate of mechanical ventilation weaning was improved in patients received early rehabilitation intervention, while its effectiveness in ECMO weaning remains unclear (12). Indeed, the successful weaning of ECMO is complex and multifactorial (13). ECMO weaning at the earliest possible time would be expected to improve outcomes, reduce cost, and optimize functional prognosis (14). This inspires us to hypothesize that if the medical rationale is based on its assumed benefits on cardiac function and oxygenation, then cardiopulmonary rehabilitation may subsequently contribute to earlier weaning of ECMO. Our perspective is to provide solutions with the application of cardiopulmonary rehabilitation and convert the aforementioned physiological changes (e.g., increased cardiopulmonary function) into patient-oriented outcomes (e.g., earlier weaning of ECMO and increased rate of ECMO weaning).

Considering the limited evidence in this aspect, ongoing innovation must move from guessing to exploring the effectiveness of cardiopulmonary rehabilitation through an adequately powered trial. Therefore, we design this multidisciplinary randomized controlled trial (RCT) to answer the following clinical question—can cardiopulmonary rehabilitation facilitate weaning of ECMO (CaRe-ECMO)? The results of this trial may subsequently provide innovative treatment solution, specifically the add-on effects of cardiopulmonary rehabilitation to the routine clinical practice for further successful weaning of ECMO.

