#### Secondary Outcomes

Secondary outcomes are listed and elaborated as follows:

1) Rate of ECMO weaning will be calculated according to date of ECMO weaning fulfilled.2) Total length of ready for ECMO weaning refers to exact length in day till patients fulfill all the criteria of ready for ECMO weaning according to daily checkout records (14).3) Total length of ECMO weaning refers to exact length in day for patients treated with ECMO therapy (29).4) Rate of mechanical ventilation weaning will be calculated according to date of mechanical ventilation weaning fulfilled. Daily screening of mechanical ventilation weaning will be strictly performed with checklist shown in Table 7 according to the American Thoracic Society and the American College of Chest Physicians Clinical Practice Guideline (30).5) Total length of mechanical ventilation refers to exact length in day for patients treated with mechanical ventilation.6) All-cause mortality is defined as rate of death due to any causes and will be calculated according to date of death (31).7) Rate of major post-ECMO complications refers to rate of complications occurred after ECMO including but not limited to ECMO-related complications (e.g., thromboembolism), mechanical ventilation-related complications (e.g., pneumonia), newly developed myocardial infarction, acute kidney injury, neurologic events (e.g., stroke, seizures), and multiple organ failure (32). Information of major post-ECMO complications will be collected in the Complication Recording Sheet (Table 8).8) Diaphragmatic thickness and mobility refer to ultrasound-guided evaluation of diaphragmatic thickness and mobility under M-mode (33).9) Extracorporeal membrane oxygenation unit LOS accounts for length in day for stay of patients in the ICU unit.10) Total hospital LOS accounts for total hospital LOS in day for stay of patients in both the ECMO unit and other departments.11) Total cost for hospitalization will be calculated by addition of the cost of all the units and department admission.12) Cerebral performance category will be recorded, for those successfully weaning of ECMO, to reflect post-ECMO neurological status (34).13) Activities of daily living will be evaluated, for those successfully weaning of ECMO, with Katz Index (35).14) Health-related quality of life will be measured, for those successfully weaning of ECMO, with SF-12 (36).

**Table 7 T7:** Mechanical ventilation weaning checklist.

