### Data Collection

Data in terms of rate of ready for ECMO weaning, rate of ECMO weaning, rate of mechanical ventilation weaning, all-cause mortality, and rate of major post-ECMO complications will be calculated throughout the index hospitalization and follow-up period (e.g., CaRe-ECMO days 7, 14, 30, and 90) according to daily evaluations recorded in the medical records. Outcomes, for instance ready for ECMO weaning, will be treated as time-to-event outcomes; therefore, date and timing of events will be also recorded to facilitate statistical analysis. Total length of ready for ECMO weaning, total length in hour of ECMO weaning, total length in day of mechanical ventilation, ECMO unit LOS, and total hospital LOS will be collected according to the medical records. CPC index, ADL score, and HRQoL score will be selectively collected among those successfully weaning of ECMO across discharge day (discharge from ECMO unit) and all follow-up time points (e.g., CaRe-ECMO days 30 and 90). In addition, diaphragmatic thickness and mobility will be evaluated with ultrasound (M-mode) every 3 days for determining the allocation of phrenic nerve and the efficacy of SEPNS. The detailed data collection schedule is given in Table 9.

**Table 9 T9:** Scheduled events and timeline of the CaRe-ECMO trial.

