### Statistical Methods

The demographic and clinical characteristics collected at randomization will be presented as means with SDs or medians with interquartile ranges for continuous variables and as percentages for categorical variables, as appropriate.

For all the outcomes, we will estimate differences in effect size between the groups on both the intention-to-treat (ITT) and per protocol (PP) basis (39). Categorical variables will be compared with the chi-square or Fisher's exact tests and continuous variables will be compared with the Student's *t*-test or the Wilcoxon signed-rank test, as appropriate. The time effect of day the time-to-event outcomes identified (e.g., rate of ready for ECMO weaning, rate of ECMO weaning, rate of mechanical ventilation weaning, all-cause mortality, and rate of major post-ECMO complications) between the groups will be estimated with the Cox proportional hazards regression analysis and graphically illustrated using the Kaplan–Meier methods until CaRe-ECMO days 7, 14, 30, and 90, respectively (40). Variables, including total length of ready for ECMO weaning, total length of ECMO weaning, total length of mechanical ventilation, ECMO unit LOS, and total hospital LOS, will be treated with time-to-event data and will be analyzed with mixed-effects ordered logistic regression (41). Secondary outcomes with normal and non-normal distributions, including CPC, ADL, HRQoL, and diaphragmatic thickness and mobility, will be estimated for group differences with mixed-effects linear regression (41).

Considering that part of patients will definitely not reach the primary endpoint, i.e., ready for ECMO weaning at CaRe-ECMO day 7 for sensitivity purpose, we will assess the heterogeneity of the treatment effect on primary outcome and secondary outcomes in pre-specified subgroups of interest as per baseline data to be collected at randomization (e.g., age, gender, main diagnosis, comorbidities, the APACHE II score, ECMO mode, length since mechanical ventilation) by using exploratory *post-hoc* sensitivity adjusted analyses for any corresponding statistical methods mentioned above.

Interim analysis will be scheduled halfway through enrollment to check that there are no serious issues with respect to sample handling or data collection.

All the analyses will be conducted at a two-sided alpha level of 5% and will be performed using the Stata version 16 (StataCorp, College Station, Texas, USA) or other software, as appropriate.

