Additional important considerations, which we addressed when preparing the CaRe-ECMO trial protocol, were the following. First, the current trial is consisting of a RCT part followed by an open-label cohort part. According to our clinical experience and retrospective data analysis, the median length of ECMO weaning varied ~from 7 to 9 days in all the types of ECMO-supported patients. The design rationale of the RCT part is to power the primary outcome, while the following open-label cohort part is dedicated to benefit patients who do not respond to one cycle of cardiopulmonary rehabilitation. This action may impair the effects of RCT on long-term outcome observation; however, it is hypothesized to provide additional opportunity for those who are probably benefitted from active intervention (56). Second, a critical concern of the CaRe-ECMO trial design is the uncertainty of the effect size of the proposed interventions. Therefore, our attention on primary outcome selection has been shifted from the exact ECMO weaning to ready for ECMO weaning. If any significant results would be introduced in terms of earlier ready for ECMO weaning or increased rate of ready for ECMO weaning due to our proposed interventions, then it may satisfy the preliminary requirements when extending its effects to more consolidated outcomes (e.g., rate of ECMO weaning). To compensate the aforementioned risks, we introduce several evidence-based checklists to ensure the standardized definition and evaluation of ECMO or mechanical ventilation weaning (Tables 5–7) and to maximally avoid potential performance bias. Third, functional outcomes are essential to the long-term recovery; therefore, CPC index, ADL score, HRQoL score, and diaphragmatic thickness and mobility will be consecutively collected. In case when primary outcome of the CaRe-ECMO trial does not show a statistically significant difference, future trials may consider to analyze our secondary clinical and functional outcomes.

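### CPC, ADL and HRQoL are compared only in patients weaned from ECMO, so these comparisons are not protected by randomisation and cannot be intention-to-treat as the plan states

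*Protocol article*

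**What the plan says.** Secondary Outcomes, items 12 to 14, limits each of the three measures to weaned patients:

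- CPC: "Cerebral performance category will be recorded, for those successfully weaning of ECMO, to reflect post-ECMO neurological status".
- ADL: "Activities of daily living will be evaluated, for those successfully weaning of ECMO, with Katz Index".
- HRQoL: "Health-related quality of life will be measured, for those successfully weaning of ECMO, with SF-12".

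Data Collection applies the same limit when the data are gathered: "CPC index, ADL score, and HRQoL score will be selectively collected among those successfully weaning of ECMO across discharge day". It then gives follow-up days 30 and 90 as examples. Table 9 marks all three measures at days 7, 14, 30 and 90 and at discharge from the ECMO unit, and does not repeat the limit.

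Statistical Methods opens with "For all the outcomes, we will estimate differences in effect size between the groups on both the intention-to-treat (ITT", and the sentence goes on to add a per-protocol basis. The same section estimates group differences in CPC, ADL and HRQoL by mixed-effects linear regression. The article gives no rule for patients who die or are never weaned.

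The Introduction names earlier weaning and a higher weaning rate as intended effects of the programme. The rate of ECMO weaning is itself a secondary outcome.

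**The concern.** Weaning happens after allocation and the programme is meant to alter it. Comparing scores among the weaned therefore conditions on a consequence of treatment. If rehabilitation weans some patients who would otherwise have stayed on ECMO, and those patients are frailer, they lower the average of the rehabilitation arm. A real benefit can then be diluted or masked, and it can even appear as harm. If selection works the other way, the error goes the other way.

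The unscored group may be large: the Introduction says "annual ECMO mortality has been reported to be approximately ranged 40–70" per cent. An analysis that omits these patients does not cover everyone randomised, so it contradicts the intention-to-treat statement.

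The Discussion says that "functional outcomes are essential to the long-term recovery" and suggests that future trials look at the secondary clinical and functional outcomes if the primary result is not significant. It also links the claim to affect standard care to superior primary and secondary outcomes. A selection effect here could mislead both the reading of this trial and the design of the next.

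**Working it through.** **The plan's own figures.** The protocol gives no sample size or effect size for CPC, ADL or HRQoL, so there is no figure to reproduce. Two inputs come from Sample Size Calculation: 183 patients per arm, and readiness for weaning at day 7 rising from 30% to 45%. The second is only a stand-in for the weaned share.

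**Assumptions not in the protocol.**
- Weaned shares are p0 (control) and p1 (rehabilitation).
- Everyone weaned under control would also be weaned under rehabilitation.
- Scores are oriented so that higher is better, with SD 1 within each type of patient.
- d is the true benefit in patients who would be weaned in either arm.
- D is how far the extra weaned patients score below the always-weaned patients of the same arm.

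**Step 1: expected weaned-only difference.** A fraction f = (p1 − p0)/p1 of weaned rehabilitation patients has no counterpart among the weaned controls. The observed difference is therefore d − D × f, and its sign reverses when D > d/f.

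At 30% versus 45%, f = 0.15/0.45 = 1/3. The number scored is 183 × 0.30 ≈ 55 versus 183 × 0.45 ≈ 82. Reversal needs D > 3d. With d = 0.2:
- D = 0.5 gives 0.2 − 0.167 = +0.03
- D = 0.75 gives 0.2 − 0.25 = −0.05
- D = 1.0 gives 0.2 − 0.333 = −0.13

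**Step 2: chance of false significant harm when d = 0.** The standard error is √[1/(183 p0) + (1 + f(1 − f)D²)/(183 p1)].

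For 30% versus 45% and D = 1, it is √[1/54.9 + 1.222/82.35] = 0.182. Then z = −0.333/0.182 = −1.83, and the chance of a result below −1.96 is 45%. Simulated t-tests in the weaned patients give about 43%.

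For 50% versus 55% and D = 1, f = 0.05/0.55 = 1/11. The standard error is √[1/91.5 + 1.083/100.65] = 0.147, z = −0.091/0.147 = −0.62, and the chance is about 9%. The rate expected with no bias is 2.5%.

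**Step 3: other weaned shares** (all assumed except the first row; normal approximation, d = 0).

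| Weaned, control vs rehabilitation | f | Reversal if | False harm, D = 0.5 | False harm, D = 1 |
|---|---|---|---|---|
| 30% vs 45% | 1/3 | D > 3d | 15.5% | 45.0% |
| 45% vs 60% | 1/4 | D > 4d | 13.3% | 37.8% |
| 40% vs 50% | 1/5 | D > 5d | 9.2% | 23.3% |
| 60% vs 70% | 1/7 | D > 7d | 7.9% | 18.6% |
| 50% vs 55% | 1/11 | D > 11d | 5.0% | 9.0% |

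Under these assumptions, equal weaned shares (f = 0) or D = 0 give no bias.

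**Step 4: a ranked comparison of everyone randomised.** Put all non-weaned patients and deaths at the bottom. At 30% versus 45% with d = D = 0, the chance that a rehabilitation patient ranks above a control patient, counting ties as half, is 0.45 × 0.70 + 0.5 × (0.45 × 0.30) + 0.5 × (0.55 × 0.70) = 0.315 + 0.0675 + 0.1925 = 0.575. In simulations with D from 0 to 1 and d of 0 or 0.2 it stayed between 0.56 and 0.58 and never reversed, with power of 67% to 82%. Part of that signal is the weaning gain itself, so this answers a different question from a mean difference in scores.

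**The case against.** The strongest reply concerns size. The 30% and 45% are readiness rates at day 7, whereas the scores are mostly taken at ECMO-unit discharge and at days 30 and 90. After day 7, non-responders in both arms are offered open-label rehabilitation (Interventions, CaRe-ECMO Group). The Discussion puts the median time to weaning at about 7 to 9 days. Both facts suggest a narrower gap in weaned shares when the scores are taken, and hence a smaller bias. This stands, and it is why the lower rows of the table matter. A narrower gap does not make the two weaned groups comparable, though.

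A reader might infer that true benefit will show up as functional harm. The documents do not support that. Neither d nor D is given, reversal needs D to be several times d, and d = 0.2 with D = 0.5 leaves the sign correct even at 30% versus 45%. The 43% belongs to one scenario.

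A reader might also infer that restricted collection puts any all-randomised comparison out of reach. That is too strong. Weaning and mortality are recorded for all patients at days 7, 14, 30 and 90, so a ranked analysis of everyone is possible with planned data. The handling of death may also be set out in an analysis plan that is not shown. What the article does state is the restriction, the between-arm test and the intention-to-treat label, and these conflict.

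Finally, these are three of fourteen secondary outcomes. The Discussion says the randomised part is there to power the primary outcome, and it concedes that the open-label stage may weaken long-term comparisons. That limits how serious the point is, but the concession does not cover selection on weaning.

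**Conclusion.** The point holds. As written, the comparisons of CPC, ADL and HRQoL condition on a post-randomisation event that the programme aims to change. They are not protected by randomisation and cannot be intention-to-treat.

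The direction and size of the bias cannot be determined from the protocol. Under the assumptions above, false significant harm with D = 1 SD and d = 0 ranges from about 43% of trials at 30% versus 45% weaned to about 9% at 50% versus 55%. These figures rest on assumed values of D and d, on everyone weaned under control also weaning with rehabilitation, and on a normal model for bounded scores.

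This should be corrected, preferably before enrolment, which Table 1 lists as not yet started. It does not threaten the primary outcome.

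**What to change.** 1. In Statistical Methods, compare the arms on these three outcomes in all randomised patients with a rank-based analysis. Place death lowest, and patients who are alive, not weaned and without a score next lowest. The weaning and mortality data needed are already collected.
2. Where feasible, also record the scores at days 30 and 90 in patients who are alive but not weaned, and amend Secondary Outcomes items 12 to 14 and Data Collection to allow it.
3. Report weaned-only scores as descriptive, beside the proportion alive and weaned in each arm, and do not label them intention-to-treat.
4. State that the day-30 and day-90 comparisons include open-label rehabilitation in both arms.
5. Reconcile the assessment times in Data Collection with those in Table 9.

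The cost is mainly wording, plus some extra assessments if item 2 is adopted. The downside is that a ranked result mixes in mortality and weaning, which are already separate outcomes, and is harder to read than a mean difference.

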**Mechanical ventilation weaning checklist**	
• Ready for mechanical ventilation weaning: Daily check prerequisite of primary disease controlled; FiO_2_ ≤ 0.6, PaO_2_/FiO_2_ > 200 with PEEP ≤ 5 cmH_2_O; no or low dose vasopressor being used; continuous intravenous sedation minimized as appropriate; response to simple questions; cough during tracheal aspirations • Should the above ready for mechanical ventilation weaning criteria fulfilled, move through the following steps when the former step is fulfilled. Should all of the steps be fulfilled indicating weaning of mechanical ventilation	
Step 1	Weaning test
	• Gradually decrease PEEP to 5 cmH_2_O with possible increase of FiO_2_ to 0.6 (over 20–30 min)
	• If: desaturation occur (SpO_2_ < 88%) and persist (>5 min) during this trial, then fail
	• If not: blood gases determined 10–20 min after establishing PEEP at 5 cmH_2_O
	• If: under these conditions (PEEP = 5 cmH_2_O and FiO_2_ at 30–60%), PaO_2_/FiO_2_ < 200, then fail
	• If not: weaning test passes, forward through the next step within 24 h
Step 2	Prolonged weaning test
	• Mechanical ventilation mode of volume-assist control ventilation or pressure support
	• Mechanical ventilation parameters of VT < 10 mL/kg; P_plat_ or pressure support < 30 cmH_2_O; RR ≤ 35/min; PEEP = 5 cmH_2_O; FiO_2_ ≤ 50%
	• If: desaturation occur (SpO_2_ < 88%) and persist (>15 min) during this trial, then failed
	• If not: prolonged weaning test passes, forward through the next step within 24 h
Step 3	Spontaneous breathing trial
	• T piece or PSV with pressure support at +7 cmH_2_O
Step 4	Weaning of mechanical ventilation

*PEEP, positive end-expiratory pressure; FiO_2_, fraction of inspired oxygen; SpO_2_, oxygen saturation; PaO_2_, partial pressure of arterial oxygen; VT, tidal volume; P_plat_, plateau pressure; RR, respiratory rate; PSV, pressure support ventilation*.

**Table 8 T8:** Complication recording sheet.

**Complication recording sheet**
Name: ___ Gender: ___ Age: ___ Inpatient ID: ___ Bed number:___ Date of record: ___ / ___ / ___, ___: ___ Main diagnosis:
**Neurological complications** **□ No □ Yes (If yes, then fill the following items)**
Date and time: ___ / ___ / ___, ___: ___
□ Cerebral hemorrhage □ Cerebral infarction □ Epileptic seizure
**Cardiovascular complications** **□ No □ Yes (If yes, then fill the following items)**
Date and time: ___ / ___ / ___, ___: ___
□ Cardiac arrest □ Newly developed myocardial infarction □ Heart failure □ Myocardium stunning (Ultrasound) □ Newly developed hypertension requiring vasodilator therapy □ Shock (□ Cardiogenic □ Hypovolemic □ Obstructive □ Distributive) □ North-south syndrome □ Tamponade (□ Blood □ Plasma □ Air)
**Respiratory complications** **□ No □ Yes (If yes, then fill the following items)**
Date and time: ___ / ___ / ___, ___: ___
□ Pneumothorax □ Pulmonary infection □ Pulmonary edema □ Pulmonary atelectasis □ Ventilator-associated lung injury
**Other complications** **□ No □ Yes (If yes, then fill the following items)**
Date and time: ___ / ___ / ___, ___: ___
Extremities complications: □ Distal ischemia □ Necrosis □ Deep venous thrombosis □ Osteofascial compartment syndrome □ Limb amputation Infection: Infection pathogen: □ G^+^ bacteria □ G^−^ bacteria □ Mycobacteria □ Fungus □ Virus and prion □ Protozoon Infection site: □ Blood □ Bone marrow □ Cerebrospinal fluid □ Ascites □ Hydrothorax □ Respiratory tract □ Skin, muscle, soft tissue □ Feces □ Urine □ Surgical site □ Wound site □ Other______ Bleeding: □ Cerebral hemorrhage □ Gastrointestinal bleeding □ Respiratory tract bleeding □ Cannulation site bleeding □ Thrombocytopenia □ Surgical site bleeding □ Hemolysis □ DIC □ Other______ Thrombosis: □ Pulmonary thromboembolism □ ECMO catheter thrombosis □ Limb thrombosis □ Mesenteric thrombosis □ Other______
**ECMO-related complications** **□ No □ Yes (If yes, then fill the following items)**
Date and time: ___ / ___ / ___, ___: ___
□ Oxygenator failure □ Raceway rupture □ Crack in connectors □ Heat exchanger malfunction □ Cannula problems □ Clots or thrombosis of circuit component □ Pump failure □ Clots hemofilter □ Circuit change □ Other______

*ID, identified number; DIC, disseminated intravascular coagulation; ECMO, extracorporeal membrane oxygenation*.

### Data Collection

Data in terms of rate of ready for ECMO weaning, rate of ECMO weaning, rate of mechanical ventilation weaning, all-cause mortality, and rate of major post-ECMO complications will be calculated throughout the index hospitalization and follow-up period (e.g., CaRe-ECMO days 7, 14, 30, and 90) according to daily evaluations recorded in the medical records. Outcomes, for instance ready for ECMO weaning, will be treated as time-to-event outcomes; therefore, date and timing of events will be also recorded to facilitate statistical analysis. Total length of ready for ECMO weaning, total length in hour of ECMO weaning, total length in day of mechanical ventilation, ECMO unit LOS, and total hospital LOS will be collected according to the medical records. CPC index, ADL score, and HRQoL score will be selectively collected among those successfully weaning of ECMO across discharge day (discharge from ECMO unit) and all follow-up time points (e.g., CaRe-ECMO days 30 and 90). In addition, diaphragmatic thickness and mobility will be evaluated with ultrasound (M-mode) every 3 days for determining the allocation of phrenic nerve and the efficacy of SEPNS. The detailed data collection schedule is given in Table 9.

**Table 9 T9:** Scheduled events and timeline of the CaRe-ECMO trial.

